### Sample Size Justification

The sample size considerations were based on the PaO_2_/FiO_2_ differences between groups obtained from comparable prospective studies [26,39,40], where EVLW indices were used as a predictor for mortality. A PaO_2_/FiO_2_ ratio difference (delta) of 48 mm Hg was detected between the groups of survivors (mean 150, SD 81) and nonsurvivors (mean 198, SD78). Based on these studies, a delta of 25 mm Hg between the groups was considered clinically meaningful and feasible for our study. Interim analysis for safety reasons will be performed after 50% (170/ 340) of patient recruitment. An independent blinded statistician would perform the interim analysis and report to the data safety monitoring committee, as only safety is the monitored outcome no alpha level modification is needed (Multimedia Appendix 4 Interim analysis and safety).

The sample size was calculated (*α*=.05; ß=.80) with a potential dropout rate of 5% (17/340), resulting in n=170 patients per arm in a total of N=340 patients (Figure 1).

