### Eligibility Criteria

The eligibility criteria for patient recruitment is shown in Textbox 1.

Inclusion and exclusion criteria for patient recruitment.Inclusion Criteria:Admitted into the emergency department.Age 18-65 years.Sepsis with a quick Sequential Organ Failure Assessment (qSOFA) score≥2 [3,14,28,33]Consent by the patient or legal guardian.Exclusion Criteria:Mechanical ventilation at screening.Unconsciousness when admitted to emergency department (with Glasgow Coma Scale score<8)Preexisting pulmonary pathology as assessed by clinical symptoms or radiographic evidence in chest x-ray or by pulmonary bedside ultrasound (>2 B lines, a comet-tail artifact)History of pulmonary disorders (chronic obstructive pulmonary disease, asthma, parenchymal lung disease, or edema) or procedures.Preexisting cardiac pathology, disease, or dysfunction (ejection fraction<50, New York Health Association class>2) lung, or cardiac surgical procedures.History of liver cirrhosis, cancer, autoimmune disease, or immunosuppression.Patients under palliative care and patients facing imminent and inevitable death in the next 30 days due to causes other than sepsisSevere burns.Advanced kidney disease (chronic kidney disease stage 4 or above)Unstable medical conditions (eg, uncontrolled diabetes, uncompensated cardiac issues, heart failure, or chronic obstructive pulmonary disease).PregnancyWith other reasons or diseases needing a restricted fluid administration

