### Randomization and Blinding

Randomization will be web-based across centers using simple randomization stratified for patient’s age and center, with 1:1 allocation. The sequence will be confidential and will be managed by a researcher independent of patient treatment. The treating physician will use the web-based randomization service—Viedoc (PCG Solutions AB). To increase the internal validity, possible confounders, such as pulmonary disorders, mechanical ventilation affecting imaging findings and bias results, kidney disease, and pre-existing cardiac disorders will be excluded by strictly implementing the eligibility criteria (Figure 1, Textbox 1, and Multimedia Appendix 2).

Patients and physicians will be unblinded to avoid endangering the patient's health and life in the situation of an emergency. However other study investigators collecting data, drawing blood samples for the analysis of PaO_2_/FiO_2_ and other parameters, and documenting, entering, or analyzing data will be blinded. Allocation concealment will be maintained until all data is collected and analyzed for the blinded personnel. The treating physician and patients will be instructed not to disclose information to the independent assessor and the data analyst. All breaches of blinding will need to be reported and documented.

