### Limitations and Contingency Planning

Our study might lead to promising results but is not without limitations. The use of surrogate markers can be seen as a limitation. Using a surrogate marker to ensure study feasibility is universal in phase 2 trials. We will plan to study hard clinical outcomes in the following phase III trial. The chosen surrogate variable of PaO_2_/FiO_2_ ratio is a central component of the SOFA score [27,41]. Higher SOFA scores are associated with higher mortality [29]. Lower PaO_2_/FiO_2_ ratio is associated with adverse outcomes in patients with sepsis [41]. Additionally, the SOFA score will be assessed to evaluate changes in the patient’s status over time since it is a core component of Sepsis-3 guidelines [14,28] and has predictive value [42]. It represents a valuable additional surrogate variable. These surrogate variables will be supplemented by other variables essential for evaluating the progress of sepsis.

We have strict inclusion and exclusion criteria in order to enhance the detectability of differences between groups and show the efficacy of the intervention if present. However, this may limit the external validity of our results and slow down the recruitment process. (Multimedia Appendix 4 Contingency Planning).

Ultrasound is an operator-dependent intervention. To standardize the ultrasound technique and interpretation, trained physicians who prove competent will perform the ultrasound. Kappa statistics will be used to assess inter-rater reliability.

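### The sample-size paragraph prints survivor and nonsurvivor oxygenation in the adverse order and gives beta as .80; both need correcting, but 170 per arm stands

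*Protocol article*

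**What the plan says.** All of the following is in the protocol article.

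- **Sample Size Justification, source data.** A PaO2/FiO2 difference of 48 mm Hg is reported as "detected between the groups of survivors (mean 150, SD 81) and nonsurvivors (mean 198, SD78"). On the strength of these studies, "a delta of 25 mm Hg between the groups was considered clinically meaningful and feasible for our study".
- **Sample Size Justification, design parameters.** "The sample size was calculated (*α*=.05; ß=.80) with a potential dropout rate of 5% (17/340"), leading to 170 per arm and 340 in total. Neither the sidedness of the test nor the SD used is named. The article nowhere says in words that power is 80%.
- **Outcomes.** A lower ratio is described as a sign of compromised oxygenation. A higher mean is expected in the intervention arm and counted as benefit.
- **Limitations and Contingency Planning.** "Lower PaO_2_/FiO_2_ ratio is associated with adverse outcomes in patients with sepsis".
- **Statistical Analysis and Randomization and Blinding.** The primary comparison is a t test on the 48-hour ratio, with 1:1 allocation.

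**The concern.** **Direction of the source data.** As printed, survivors average 150 and nonsurvivors 198, so a higher ratio goes with death. That is the reverse of the prognostic relation on which the Outcomes and Limitations sections rely. It matters because this is the only numerical link between the ratio and mortality that the article shows, and the 25 mm Hg delta is said to be based on it.

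**The error rate.** Beta is the probability of missing a true effect. A beta of .80 declares a trial with a 20% chance of detecting its planned difference. Anyone who copies the parameters into a registry entry or an ethics submission, or tries to reproduce the calculation, will either repeat a wrong power or fail to arrive at 170.

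**Working it through.** **Inputs.** From the Sample Size Justification: alpha .05, delta 25 mm Hg, SDs 81 and 78, dropout 5%. From Randomization and Blinding: 1:1 allocation. From Statistical Analysis: t test. Assumed because not stated: a two-sided test, and a planning SD equal to the pooled value of the two quoted SDs.

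Pooled SD = √[(81² + 78²)/2] = √[(6561 + 6084)/2] = √6322.5 ≈ 79.5.

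**Formula.** Evaluable n per arm = 2(z₁₋α/₂ + z_power)² × SD² / delta². Randomized n per arm = evaluable n / 0.95. Each result was also checked with the exact noncentral t distribution.

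**Step 1: reproduce 170, reading .80 as power.**

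2 × (1.960 + 0.842)² × 6322.5 / 625 ≈ 158.8, so 159 evaluable per arm (exact t: 160). Dividing by 0.95 gives 168 (exact t: 169). The stated 170 is reproduced to within one or two patients.

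| SD | Evaluable per arm, normal (exact t) | Randomized per arm, normal (exact t) |
|---|---|---|
| 78 | 153 (154) | 162 (163) |
| 79.5 | 159 (160) | 168 (169) |
| 81 | 165 (166) | 174 (175) |

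The stated 170 lies inside the range given by the article's own SDs. A one-sided test at 80% power would give only 128 to 138 randomized per arm over the same SDs, so the calculation was evidently two-sided.

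**Step 2: read beta = .80 literally (power .20, so z_power = −0.842).**

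2 × (1.960 − 0.842)² × 6322.5 / 625 ≈ 25.3, so 26 evaluable per arm (exact t: 27), or 28 to 29 after dropout. This is far from 170.

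**Step 3: power of the planned trial.**

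With 5% dropout, 170 × 0.95 = 161.5 evaluable per arm. At SD 79.5 and delta 25, 161 per arm give power 80.5% (exact t: 80.3%). All 170 evaluable would give 82.6% (exact t: 82.4%).

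**Step 4: effect of exchanging the two labels.**

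The source difference is |198 − 150| = 48 in either order. The calculation uses the separately chosen delta of 25 and the pooled SD, and neither depends on which group is called survivors. N is unchanged. Delta 48 was not the planning value: at 80% power it would need only 44 evaluable, or 47 randomized, per arm.

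**Step 5: direction, side by side.**

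- Sample Size Justification: lower mean (150) in survivors, higher mean (198) in nonsurvivors.
- Outcomes: a lower ratio means compromised oxygenation; a higher mean is the expected benefit.
- Limitations and Contingency Planning: a lower ratio goes with adverse outcomes.

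The first cannot be reconciled with the other two as printed, and nothing in the article corrects it.

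**The case against.** The strongest defence is that both errors are slips of the pen. N=340 itself shows that 80% power was used, the reversed means do not enter the calculation, and the direction of the hypothesis is fixed in the Outcomes section. The ratio is also justified elsewhere, through its inverse correlation with B lines and its place in the SOFA score. All of that stands. It limits the point to the text, but it does not make the two printed figures right.

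Three stronger readings are tempting and are not supported:

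- *The inputs contradict 170 per arm, or the trial is underpowered.* Only the literal beta symbol conflicts with 170. The other printed inputs reproduce it.
- *The surrogate points the wrong way.* One line runs against several consistent statements, and exchanged labels would explain it. Whether the source data really run that way cannot be judged without the source.
- *The SD is too small for this population.* The trial excludes patients ventilated at screening and those with existing lung pathology, so one may ask whether an SD near 80 carries over. The article gives no other SD, however, and nothing in it shows that the SD would be larger. The Limitations section says the strict criteria are meant to make differences easier to detect, so a smaller SD is just as arguable. Nor is the planning SD absent in substance: the two printed SDs suffice to recover it.

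**Conclusion.** Two stated figures are wrong as printed: the order of the survivor and nonsurvivor means, and beta given as .80. The second, taken literally, declares 20% power and about 27 evaluable patients per arm. Read as 80% power, the paragraph is coherent: 168 to 169 randomized per arm are required and 170 are planned, with about 80% power after 5% dropout.

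The damage is to the stated rationale and the stated power, not to the size of the trial. The conclusion assumes a two-sided test and the pooled SD of 79.5. That the labels were exchanged is probable but unconfirmed.

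**What to change.** 1. Check the two means against the cited study. If the labels are exchanged, correct them. If they are not, remove this contrast as support for the 25 mm Hg delta and for the ratio as a surrogate, and rest both on other grounds.
2. Restate the design parameters as: two-sided alpha .05, power 80% (beta .20), delta 25 mm Hg, pooled SD 79.5, about 160 evaluable and 170 randomized per arm allowing for 5% dropout.

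The cost is a text correction and one look at the source. Sample size, delta, test and analysis stay as they are. According to the Results section, funding and ethical approval were still being sought and registration was still to come, so the corrected wording can go into those submissions. Reporting the blinded pooled SD at the planned 170-patient interim would be a useful check on the planning SD, but it is optional and not part of this correction.

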### Statistical Analysis

The primary outcome will be PaO_2_/FiO_2_, a continuous variable. Mean (SD) will be reported after testing for normality, and then will be analyzed via *t* test. For secondary outcomes, a repeated measure ANOVA and *t* test will be used for analysis of continuous data. Categorical data will be reported using proportions and will be analyzed using chi-square test.

All analysis will be conducted according to the principle of intention-to-treat, and multiple imputation technique will be used to account for missing data. A subgroup analysis will be performed based on randomization of age, site, and severity of sepsis. An intention-to-treat analysis approach will be used in this study (Multimedia Appendix 4 Missing Data).

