**Enrollment**										
	Eligibility screening	X								
	Informed consent	X								
	Registration form	X								
	Baseline assessment (clinical features): sepsis with a qSOFA^b^ score≥2; low systolic blood pressure≤100 mmHg; respiratory rate≥22 breaths per minute; altered mentation with Glasgow coma scale score<15		X							
	Baseline assessment (laboratory parameters): ultrasound; PaO_2_/FiO_2_; arterial blood gas analysis; x-ray, NT-proBNP		X							
	Allocation		X							

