### Outcomes

The primary outcome is the oxygenation (measured as mean PaO_2_/FiO_2_) at 48 hours after IV fluid administration. We expect a higher mean of PaO_2_/FiO_2_ in the intervention arm, which will be considered beneficial. A lower PaO_2_/FiO_2_ ratio is a sign of oxygenation compromise, which can occur with excessive fluid administration and increased EVLW. We will use PaO_2_/FiO_2_ ratio because it is a reliable and commonly used index of oxygenation that is easy to obtain and clinically significant as a predictor for mortality in patients with sepsis [26,35]. Arterial blood samples will be obtained for PaO_2_ measurement. FiO_2_ will be estimated based on widely accepted approximated values for those patients not mechanically ventilated [36].

The secondary outcomes will be assessed at time points of 0, 6, 12, 24, and 48 hours and after 15mL/kg of fluid administration, and also at 30 days. We will then evaluate (1) means of PaO_2_/FiO_2_ ratio between groups at these time points, (2) the incidence of pulmonary outcomes (pulmonary edema, acute respiratory distress syndrome, or need for invasive mechanical ventilation), (3) mean SOFA score, (4) mean creatinine level (in milligram per deciliter), (5) mean amount of volume of administered fluid, and (6) proportion frequency of 30-day mortality. Additionally, the type of IV fluid will be documented (Table 1).

Pulmonary outcomes (namely, pulmonary edema) will be confirmed by physicians based on symptoms and signs (eg, shortness of breath after fluid resuscitation and crackles), laboratory parameters (raised NT-proBNP, adjusted for age [37]), and x-ray findings suggestive of pulmonary edema.

The outcomes will be measured and documented in data collection forms by a nurse from the participating center. These forms will be made available in the protocol. Reliability and validity of laboratory tests at different participating centers will be made available in the protocol.

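### The primary 48-hour PaO2/FiO2 comparison is an unadjusted t test; adjusting for the 0 h value, age and centre would gain precision at almost no cost

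*Protocol article*

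**What the plan says.** The Outcomes section defines the endpoint as a value at one time and not as a change from baseline: "The primary outcome is the oxygenation (measured as mean PaO_2_/FiO_2_) at 48 hours after IV fluid administration". The Statistical Analysis section then fixes the test: "Mean (SD) will be reported after testing for normality, and then will be analyzed via" a t test. Neither section names a covariate or an adjusted sensitivity analysis.

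Two other parts of the protocol bear on this:

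- Table 1 lists the oxygenation ratio among the baseline measurements: "Baseline assessment (laboratory parameters): ultrasound; PaO_2_/FiO_2_; arterial blood gas analysis; x-ray, NT-proBNP". Its assessment rows also mark PaO2/FiO2 at 0 h.
- Randomization and Blinding describes "simple randomization stratified for patient’s age and center, with 1:1 allocation". In the analysis text these factors return only here: "A subgroup analysis will be performed based on randomization of age, site, and severity of sepsis".

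For the serial data, the Statistical Analysis section says "For secondary outcomes, a repeated measure ANOVA" and t test will be used for continuous variables. The Outcomes section includes 0 h in its list of secondary assessment times.

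**The concern.** Baseline oxygenation is the natural predictor of oxygenation two days later, and centres can be expected to differ. A t test on the 48-hour value leaves both sources of variation in the error term, although the trial will already hold the data needed to remove them.

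At stake is the chance of detecting the targeted difference and the width of the confidence interval. The sample size is set at 80% power with almost nothing in reserve, so the choice of analysis matters more than it would in a generously sized trial. The protocol's limitations section says that strict eligibility is meant to make group differences easier to detect, and accepts narrower generalisability and slower recruitment for it. Covariate adjustment serves the same aim without either cost.

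**Working it through.** **Inputs.** From Sample Size Justification: difference 25 mm Hg; SDs 81 and 78, taken here as 80; alpha 0.05, read as two-sided; power 80%; dropout 5%; 170 per arm. Evaluable patients per arm: 170 × 0.95 = 161.5. The correlation rho between the 0 h and 48-hour values is not in the protocol; the range 0.2 to 0.7 is an assumption.

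**Step 1: reproduce the plan's sample size.**

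n per arm = 2 × (1.960 + 0.842)² × 80² / 25² = 160.8, rounded up to 161.

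With dropout: 161 / 0.95 = 169.5, rounded up to 170 per arm and 340 in total.

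This matches the protocol exactly. The pooled SD of 79.5 gives 168 per arm. A one-sided test or 90% power does not reproduce 170. The stated size is therefore that of an unadjusted two-sided comparison.

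**Step 2: precision and power of the t test.**

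SE = 80 × √(2/161.5) = 8.90 mm Hg.

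95% half-width = 1.967 × 8.90 = 17.5 mm Hg.

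Power ≈ Φ(25/8.90 − 1.967) = Φ(0.84), about 80%.

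**Step 3: adjust for the 0 h value.** ANCOVA replaces the SD by 80 × √(1 − rho²). The few degrees of freedom used by the covariates are ignored.

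| rho (assumed) | Residual SD | SE | 95% half-width | Power | Evaluable per arm for 80% |
|---|---|---|---|---|---|
| 0 (t test) | 80.0 | 8.90 | 17.5 | 80% | 162 |
| 0.2 | 78.4 | 8.72 | 17.2 | 82% | 156 |
| 0.3 | 76.3 | 8.49 | 16.7 | 84% | 148 |
| 0.5 | 69.3 | 7.71 | 15.2 | 90% | 122 |
| 0.7 | 57.1 | 6.36 | 12.5 | 98% | 83 |

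The last column solves the t-test power equation, which gives 162 at rho = 0 where the normal formula in Step 1 gives 161. At rho 0.5 the chance of missing a true 25 mm Hg difference falls from about 20% to about 10%.

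**Step 4: the strata.** Suppose age and centre explain a share R² of the variance and the allocation forces balance within strata. The t test's actual type I error is then 2 × [1 − Φ(1.96/√(1 − R²))]: 4.4% at R² = 5% and 3.9% at R² = 10%. At SD 79.5 and 161 per arm, power is 82.5% and 84.5% with adjustment for the strata, against 81.1% and 81.8% without. Both R² values are assumptions, and so is forced balance.

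**Step 5: the serial PaO2/FiO2 analysis.** There are five scheduled times (0, 6, 12, 24 and 48 h). The expected difference at 0 h is zero. If 0 h enters as an outcome and the group main effect is tested, a constant effect of 25 mm Hg from 6 h onwards averages to (0 + 4 × 25)/5 = 20 mm Hg, a dilution of one fifth.

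**The case against.** The strongest reply is that nothing here is invalid. In a 1:1 randomised trial the two-sample t test is unbiased and controls its error rate, which already allows for chance baseline imbalance. The sample size was built for that test, and Step 1 confirms that the two match. This stands. A reader might infer from the missing adjustment that the result would be biased or the trial underpowered by its own standard; the protocol supports neither inference.

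The second reply is that the gain depends on an undocumented correlation. Eligibility excludes ventilated patients, prior lung and cardiac disease, and more than two B lines, which narrows the baseline range. FiO2 is approximated in patients who are not ventilated, which adds noise. Both could lower rho, and at 0.2 the gain is only about 2 percentage points. This also stands: the direction is secure and the size is not.

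Three stronger readings are tempting but go beyond the text:

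- **Standard errors that are too wide.** This requires allocation that balances within strata. The protocol speaks of simple randomisation with stratification and mentions no blocks or minimisation. Simple allocation within strata does not force balance, and the t test then keeps its nominal size.
- **A diluted secondary analysis.** The protocol does not say whether 0 h enters the repeated-measures ANOVA, or whether the main effect or the group-by-time interaction is tested. Dilution is a risk to rule out, not an established flaw.
- **A harmful normality test.** No alternative procedure is named if normality fails, so the test has no stated consequence for the primary analysis and is not part of this point.

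Finally, a condensed article may leave model details to a fuller document. That would excuse silence about the method, but the article is not silent: it names the test.

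**Conclusion.** The point holds as a recommended improvement in efficiency. The protocol fixes an unadjusted primary test while collecting the baseline value and stratifying on two factors that the test does not use.

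Adjusting for the 0 h value would raise power from about 80% to between about 82% and 98% over assumed correlations of 0.2 to 0.7. The gain is small at the lower end and material around 0.5. These figures rest on a 25 mm Hg difference, SD 80 and 161.5 evaluable patients per arm. Adjusting for age and centre adds a little more if those factors predict the outcome. It also avoids conservative standard errors if the allocation does balance within strata, which the protocol leaves unclear.

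The secondary point is one of clarity: the role of 0 h in the serial analysis should be stated.

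**What to change.** In Statistical Analysis:

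1. Make the primary analysis an ANCOVA of 48-hour PaO2/FiO2 on arm, 0 h PaO2/FiO2, age (or age stratum) and centre. Pool centres or fit them as a random effect if some are small. Report the adjusted mean difference with its 95% confidence interval.
2. Include the same terms in the multiple-imputation model.
3. Keep the unadjusted t test as a sensitivity analysis, and leave N at 340.
4. For the serial PaO2/FiO2 data, state that 0 h is a covariate and not an outcome time point, and say which term is tested. A mixed model on the 6 to 48 h values would do this.
5. In Randomization and Blinding, say whether allocation within strata is balanced, for example by blocks.

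The cost is about a paragraph of text, with no extra patients or measurements. According to the Results section, centres are still being selected and the trial is not yet registered, so the change can be made before enrolment.

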Observational studies suggest that the number of B lines correlates with the amount of EVLW. There is an inverse correlation between the number of B lines and oxygenation measured as the ratio of the partial pressure of arterial oxygen (PaO_2_) to the fraction of inspired oxygen (FiO_2_) [26]. The PaO_2_/FiO_2_ ratio is an integral part of the Sequential Organ Failure Assessment (SOFA) score, a score to assess and diagnose sepsis severity [14,27,28]. Elevated SOFA scores are associated with higher mortality in patients with sepsis [29]. However, lung ultrasound for guiding individualized fluid treatment in sepsis has never been tested in a randomized controlled setting.

We propose to limit the initial fluid volume in the treatment of patients with sepsis in the emergency department by detecting EVLW with lung ultrasound. This approach could enable physicians to better assess and meet individual fluid needs of patients with sepsis. This proposal may also lead to an improved therapy regimen for initial sepsis treatment that avoids administration of excess fluid volume, in turn, limits the consequent damage and decreases mortality in this high-risk group.

Therefore, we plan a randomized controlled trial with the primary objective to assess if fluid administration guided by bedside lung ultrasound can lead to an improved oxygenation (PaO_2_/FiO_2_) 48 hours after fluid administration than that in the current standard of care fluid administration in adult patients with sepsis in the emergency department.

Secondary objectives are to determine whether fluid administration guided by bedside lung ultrasound positively impacts the course of treatment after 15 mL/kg fluid at 0, 6, 12, 24, and 48 hours. These objectives will be evaluated by PaO_2_/FiO_2_ ratio, pulmonary outcomes (pulmonary edema, acute respiratory distress syndrome, or the need for invasive mechanical ventilation), the severity of sepsis (SOFA score), kidney function (mean creatinine level), the volume of administered fluid, and 30-day mortality.

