### Intervention

Trained physicians will perform lung ultrasound following the Bedside Lung Ultrasound in Emergency (BLUE) protocol technique [34]—an ultrasound protocol to identify points at the thoracic cage of patients using both hands of the investigator (Figure 2)—to identify pulmonary edema by the appearance of B lines [26].

Panel A shows a patient with sepsis admitted to the emergency department. Patient will be surveyed for eligibility and will accordingly receive either fluid limited by lung ultrasound or 30 mL/kg (ie, the control group). Ultrasound will be performed as per the BLUE protocol. Panel B shows how to identify points on the thoracic cage of a patient through morphological examination using both hands: little finger of the upper hand is just below the clavicle, fingertips at middle line, and the lower hand below the upper hand. The upper BLUE-point is at the middle of the upper hand, and the lower BLUE-point is at the middle of the lower palm, creating 4 points in both hemithoraxes. At these points (1-4, as shown in panel C), ultrasound will be conducted and fluid will be given until 3 B lines appear in the ultrasound. BLUE protocol defines B lines as those vertical and echogenic narrow-based lines that widen progressively as they pass to the other end of the image [25,34].

A phased array (1-5 MHz) transducer will be used. The images will be acquired while the patient is in a supine position, saved, and coded for further quality control and assessing inter-rater reliability. A baseline lung-ultrasound scan to assess the extent of B lines (Figure 2) will be performed. Subsequently, the resuscitation target in the intervention arm will be determined or limited by lung ultrasound as follows (Figure 1). Repeated ultrasound scan will be performed after the initial 15 mL/kg IV fluid bolus in the intervention arm and then after every 500 mL of fluid administration. If 2 B lines appear, scans will be performed after every additional 300 mL of fluid in the intervention arm. When 3 or more B lines are present bilaterally in more than 2 areas, further fluid administration will be stopped. Therefore, fluid resuscitation target for the intervention group is to administer volume until the appearance of 3 B lines (Figure1). If a further hemodynamic compromise is detected in the intervention arm following IV fluid discontinuation, vasopressors will be started or continued as per the Sepsis-3 guidelines (Figure 1).

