The control arm will be assessed by a baseline lung ultrasound to document the absence of B lines and will then receive at least 30 mL/kg fluids as per the Sepsis-3 guidelines. After the initial bolus, the type and rate of IV fluid administration will be left to the discretion of the treating physician and the local emergency departments’ protocols. All concomitant care and interventions are permitted during the trial.

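### Secondary outcomes are compared between arms at 0 h and after 15 mL/kg, before assigned fluid differs; an ANOVA group main effect that includes these times would be diluted

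*Protocol article*

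**What the plan says.** The Outcomes section sets the times: "The secondary outcomes will be assessed at time points of 0, 6, 12, 24, and 48 hours and after 15mL/kg of fluid administration", with a further assessment at 30 days. The first secondary outcome is then the mean PaO2/FiO2 "ratio between groups at these time points". For continuous secondary outcomes the Statistical Analysis section gives the method as "For secondary outcomes, a repeated measure ANOVA and" t test. It does not name the ANOVA term that carries the treatment comparison, and it gives the 0 h value no role as a covariate.

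Three other places show what the two early times are:

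- Table 1 puts allocation at 0 h, together with the row "Baseline assessment (laboratory parameters): ultrasound" and the baseline blood gas. The table is broken in the text at hand, so this column placement is a reading of it.
- The Intervention section says "Repeated ultrasound scan will be performed after the initial 15 mL/kg IV fluid bolus in the intervention arm". That is the first scan after fluid starts.
- The same section says that control patients have a baseline scan and "will then receive at least 30 mL/kg fluids as per the Sepsis-3 guidelines".

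The 15 mL/kg time is worded in more than one way. Outcomes adds it to the clock times as a separate occasion. The Introduction has "after 15 mL/kg fluid at 0, 6, 12, 24, and 48 hours", which can be read as making it the anchor of the clock, and the Abstract is similar but omits 0 h. Table 1 has no column for it.

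**The concern.** A between-arm comparison is informative only once the arms can differ. At 0 h no trial fluid has been given, so a t test there is a significance test of baseline in a randomized trial, and any significant result is chance. At 15 mL/kg the intervention arm has just finished its fixed first bolus, and a control patient on the way to at least 30 mL/kg has been assigned the same volume. The accurate statement is that assigned volume does not yet differ. Care is open-label, so the documents do not rule out every other difference.

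The consequence for the ANOVA depends on a choice that the article leaves open. The group main effect compares each patient's average over all occasions in the model, so occasions with no expected difference pull the estimate towards zero. The 0 h value would serve better as a covariate, where it adds precision. The analyses at stake are secondary PaO2/FiO2, SOFA and creatinine, in a trial whose results are meant to inform the design of later ones.

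**Working it through.** **Inputs from the article.** Difference 25 mm Hg ("a delta of 25 mm Hg between the groups was considered clinically meaningful and feasible for our study"); SDs 81 and 78 from the cited groups; α 0.05; power 0.80 (printed as β); 5% dropout; 1:1 allocation; 170 per arm. The article gives no power figure for the secondary analyses.

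**The plan's own figure.** Pooled SD = √((81² + 78²)/2) = 79.5. With n = 2(1.960 + 0.842)²·SD²/25², two-sided:

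- SD 79.5 gives 159 per arm, and 159/0.95 gives 168.
- SD 80 gives 161 per arm, and 161/0.95 gives 170, the stated number.

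The sample size reproduces, with 161 evaluable per arm.

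**Assumptions not in the article.** The effect is 25 mm Hg at each of 6, 12, 24 and 48 h, and zero at 0 h and after 15 mL/kg. SD is 79.5 at every occasion. Within-patient correlation ρ is equal across occasions, at 0.3, 0.5 or 0.7.

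**Group main effect.** With m occasions, k of them null:

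- expected difference = 25(m − k)/m
- SD of a patient's mean = 79.5·√((1 + (m − 1)ρ)/m)
- SE = that SD × √(2/161)

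Worked for ρ = 0.5:

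- Six occasions, two null: 25 × 4/6 = 16.7; SD 60.7; SE 6.77; ratio 2.46; power 0.69.
- Five occasions, 0 h null: 25 × 4/5 = 20.0; SD 61.6; SE 6.87; ratio 2.91; power 0.83.
- 6–48 h only: 25; SD 62.9; SE 7.01; ratio 3.57; power 0.95.

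| Occasions averaged | Expected difference (mm Hg) | Power, ρ = 0.3 | ρ = 0.5 | ρ = 0.7 |
|---|---|---|---|---|
| 0 h, after 15 mL/kg, 6–48 h | 16.7 | 0.83 | 0.69 | 0.58 |
| 0 h, 6–48 h | 20.0 | 0.93 | 0.83 | 0.74 |
| 6–48 h only | 25.0 | 0.98 | 0.95 | 0.89 |

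With the 0 h value as covariate, the variance factor for the 6–48 h mean becomes (1 + 3ρ)/4 − ρ². Power is then at least 0.995 at all three correlations.

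**Group-by-time test.** The noncentrality is (161/2)·Σ(effect − mean effect)²/(79.5²(1 − ρ)). For six occasions the sum is 2 × 16.7² + 4 × 8.3² ≈ 833, which at ρ = 0.5 gives 21.2 on 5 degrees of freedom. Power is 0.87/0.96/0.999 at ρ = 0.3/0.5/0.7. With 0 h as the only early occasion it is 0.67/0.83/0.97. With 6–48 h alone, a constant effect produces no interaction and the rejection rate is 0.05. This test is not diluted; it needs an early occasion to detect a constant later effect.

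**Separate t tests.** Each uses one time. At 6, 12, 24 or 48 h, SE = 79.5·√(2/161) = 8.86, 25/8.86 = 2.82, and power is 0.81, whatever is done at the early times. Two null tests at 0 h and 15 mL/kg carry a 1 − 0.95² = 9.75% chance of at least one false positive per outcome if they were independent.

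**The case against.** The strongest reply is that the dilution is conditional. No ANOVA term is named. With baseline among the occasions, group-by-time is the usual treatment test, and the working shows that it keeps high power when both early times are included. The t tests, the other half of the stated method, lose nothing at 6–48 h. A reader might infer that every secondary analysis is diluted; the documents do not support that.

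Four further points limit the concern:

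- **Linear growth to 25 mm Hg at 48 h.** A reader might set the low power of the six-occasion average in this case (about 21% at SD 80, ρ = 0.5) against the 90% of a baseline-adjusted 48 h contrast. These are unlike tests. Dropping both null occasions raises the unadjusted main effect only to about 38%, because most of the loss comes from averaging small early effects. Group-by-time has about 75% there.
- **Missing rows.** Repeated-measures ANOVA needs complete data, but the Statistical Analysis section plans multiple imputation, so this is no separate fault.
- **The 15 mL/kg occasion.** The six-occasion case requires it to be separate, as in Outcomes. The Introduction, Abstract and Table 1 leave that open. With five occasions, power at ρ = 0.5 is 0.83.
- **Level of detail.** The ANOVA term, covariates and covariance structure are commonly left to an analysis plan, so their absence alone is no finding.

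All of this stands. What survives is stated text: between-group comparison of means at 0 h and after 15 mL/kg, before assigned volume differs.

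**Conclusion.** The point holds in a limited form. Between-arm tests at 0 h and after 15 mL/kg are uninformative as specified. If the ANOVA group main effect is the treatment test, including these times shrinks a constant later effect by one fifth (0 h only) or one third (both). At ρ = 0.5, power falls from 0.95 to 0.83 or 0.69. These figures rest on the assumed constant effect, equal correlation, SD 79.5 and 161 per arm; the two-occasion figure also rests on a separate 15 mL/kg occasion.

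The primary analysis is a t test at 48 h alone, so neither it nor the total of 340 patients is affected. This is a correction to the secondary analyses and no threat to the trial's main conclusion.

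**What to change.** For secondary PaO2/FiO2, SOFA and creatinine, compare the arms on the 6, 12, 24 and 48 h values in a repeated-measures mixed model with arm, time, arm-by-time, the 0 h value as covariate and the randomization strata (age, center). Report the arm difference with a 95% confidence interval at each time. Do not rest the conclusion on the omnibus arm-by-time test in this model: without an early occasion it cannot detect a constant effect.

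Show the 0 h and post-15 mL/kg values descriptively, without between-arm tests. Reconcile the Abstract, Introduction, Outcomes and Table 1 on whether 15 mL/kg marks a separate assessment or anchors the clock times.

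The cost is analysis wording only. The 0 h values are already scheduled, and no extra patients or measurements are needed.
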